### Drug adherence and compliance

Drug adherence is expected to be good, owing to the short study duration of 5 days and three visits after recruitment. Measures taken to maximize adherence include careful screening, fully informing patients of the potential benefits and risks, and attentive follow-up. Compliance will be checked by patients’ documented daily diaries, reporting how many sprays and times they apply the study medication, and by weighing each dispensed aerosol on the date on which the study medication is issued, and again on the date on which it is returned by the patient.

### Outcome measures

#### Primary outcome measures

Time to complete resolution of sore throat, i.e., length of time from the start of treatment until complete resolution. Sore throat will be assessed using an 11-point (0 to 10) numeric visual analog scale, with 0 indicating ‘no pain’ and 10 indicating ‘worst possible pain’. This score will be evaluated thrice daily, immediately before spraying. Complete resolution of sore throat is defined as a reduction of the score to 1 or less, lasting for more than 24 hours [21].Relief rate of sore throat: this is defined as a reduction by 50 % in the baseline visual analog scale score recorded prior to treatment (day 0), lasting for more than 24 hours. The relief rate of sore throat is the proportion of patients who achieve relief of sore throat.

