### Interventions

All participants are randomly allocated to one of three parallel treatment groups: (1) QWQYA with the current propellant, three sprays into the pharyngeal region thrice daily; (2) QWQYA with the previous propellant, three sprays into the pharyngeal region thrice daily; and (3) the placebo aerosol, three sprays into the pharyngeal region thrice daily. The scheduled treatment duration will be 5 consecutive days.

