### Sample size calculation

The sample size was calculated on the basis of the two primary outcomes, using ‘Non-inferiority tests for two proportions [differences]’ in PASS 11.0. Based on a previous study [22], the mean time to complete resolution of sore throat in both active treatments was similar, both with a standard deviation of 2.2 days. A difference of 1 day or more between groups was regarded a clinically important effect. Setting a one-sided *α* of 0.05 and *β* of 0.1, the sample size was estimated to be 84 cases for each group. Based on consultation with clinical experts and a preliminary unpublished study provided by the sponsor, the relief rate of sore throat in QWQYA with previous propellant was estimated at 91 %, with a difference of 10 % or more considered clinically significant. The sample size was estimated at 118 participants for each group, assuming a one-sided *α* of 0.05 and *β* of 0.15. Both the sample sizes were calculated according to the formula:

*n* = $$ {\left[\frac{2\left({Z}_{1-\alpha /2}+{Z}_{\beta}\right)\sigma }{\delta -\varDelta}\right]}^2 $$

Therefore, the final sample size for each group was 118 participants. Taking approximate dropout rates of 20 % into account, the number of participants to be recruited was estimated at 140 per group. Therefore, a total of 420 patients will be recruited in this trial.

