### Statistical analysis

An independent statistician will perform statistical analysis using SAS 9.3. The full analysis set population includes all randomized participants as allocated. Only missing data regarding the primary outcomes will be adjusted using the last observation carried forward method. The per-protocol population includes only patients who fulfil the protocol. Analysis of efficacy will be performed based on the full analysis set and per-protocol population. Safety analyses will be performed in those populations, which include all randomized participants who receive at least one spray of medication and who have at least one visit for safety, whether or not they are withdrawn prematurely.

A fully specified statistical analysis plan will be written before unmasking. Quantitative variables will be described as mean ± standard deviation or median, and qualitative variables as frequency and percentage. Baseline analyses will be performed using analysis of variance (ANOVA) or rank-sum test for quantitative data and chi-squared or Fisher’s exact test for qualitative data. A non-inferiority test will be used to compare the two active QWQYA groups, and a superiority test to compare the current-propellant QWQYA group and the placebo group. A one-sided confidence interval method will be used in efficacy analyses. Statistical significance will be considered for *P* ≤ 0.05.

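### The 5-day scoring window censors time to complete resolution, but the outcome is sized as a complete mean with LOCF, which can inflate the false non-inferiority rate above 5%

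*Protocol article*

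**What the plan says.** **Event.** Under Primary outcome measures: "Complete resolution of sore throat is defined as a reduction of the score to 1 or less, lasting for more than 24 hours". The clock starts with treatment, and the 0-to-10 score is taken three times a day, just before each spraying.

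**Window.** Under Interventions: "The scheduled treatment duration will be 5 consecutive days". Drug adherence and compliance also gives a study duration of 5 days.

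**Unresolved patients are expected.** Resolution rate is a secondary outcome. The data management section provides for treatment after the trial for those not yet cured. Patients who take other remedies for the sore throat are withdrawn, and the sample size allows for about 20% dropout.

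**Planning.** The sample size section takes the average time as alike in the two active arms, "both with a standard deviation of 2.2 days". It counts a gap of at least 1 day as clinically important and, at a one-sided 5% level with 90% power, arrives at 84 per group. The mean itself is not given.

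**Analysis.** The two active arms are compared by a non-inferiority test with a one-sided confidence interval. On missing values: "Only missing data regarding the primary outcomes will be adjusted using the last observation carried forward method". No test is named for the time outcome, and a full analysis plan is promised before unmasking.

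**The concern.** A time to event seen through a short window is right-censored. A patient still in pain at the end has a resolution time known only to exceed the window. A patient whose pain goes in the last day has an onset that the rule of more than 24 hours cannot confirm. The protocol's stated elements, namely a mean, an SD, a margin in days and LOCF, all treat the time as complete.

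This matters most for non-inferiority. Setting unresolved times to the window's end hides more of the delay in the slower arm than in the faster one. The observed difference shrinks while the margin stays at 1 day, so the error favours a declaration of non-inferiority for the current propellant.

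LOCF adds a second problem. If scores are carried forward, a patient who drops out after one score of 1 or less acquires a resolution of more than 24 hours that was never recorded. If the event time is what is missing, an unresolved patient has nothing to carry forward.

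**Working it through.** **1. The planned figure.** The usual formula for non-inferiority of two means, with equal true means, is n = 2(z₀.₉₅ + z₀.₉₀)²σ²/margin². With z = 1.645 and 1.282, σ = 2.2 and margin 1:

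n = 2 × (2.927)² × 4.84 / 1 ≈ 82.9, so 83 per group; the t-based version gives 84.

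The stated 84 is thus the size for a complete mean, with the 1 day acting as the non-inferiority margin.

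**2. The last confirmable onset.** Scoring is tied to spraying over 5 days. An onset needs more than 24 hours of later scores, so the limit is about 5 − 1 = day 4. A day-5 cap is the lenient alternative.

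**3. Inputs for the error rate.**
- From the protocol: SD 2.2 days in each arm, margin 1 day, one-sided 0.05, 118 evaluable per arm.
- Assumed: gamma-distributed times; reference mean 2, 3 or 4 days; new product truly 1 day slower; unresolved patients set to the cap.

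With d the capped mean difference and SE = √[(s₁² + s₂²)/118], non-inferiority is declared with probability Φ((1 − 1.645·SE − d)/SE).

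**4. Check without a cap.** SE = 2.2 × √(2/118) = 0.286 and d = 1, which gives Φ(−1.645) = 5%, as intended.

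**5. One case in full: reference mean 3, day-5 cap.** The mean of min(T, 5) is the integral of the gamma survival function from 0 to 5.
- Capped means 2.69 and 3.49, so d = 0.80
- Capped SDs 1.53 and 1.34, so SE = √[(2.34 + 1.80)/118] = 0.187
- Pass if the observed difference is below 1 − 1.645 × 0.187 = 0.69
- Probability Φ((0.69 − 0.80)/0.187) ≈ 28%

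**6. All cases** (simulation, 6,000 trials each; the formula in step 3 agrees to about one percentage point):

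| Reference mean (days) | Unresolved at day 5, reference / slower arm | Difference left, day-5 cap | False non-inferiority, day-5 cap | Difference left, day-4 cap | False non-inferiority, day-4 cap |
|---|---|---|---|---|---|
| 2 | 9% / 16% | 0.90 | 11% | 0.81 | 28% |
| 3 | 16% / 27% | 0.80 | 28-29% | 0.66 | 75% |
| 4 | 27% / 44% | 0.65 | 72% | 0.46 | nearly 100% |

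**7. Sensitivity.** Lognormal times give similar figures. Setting onsets after day 4 to day 5 gives 9%, 21% and 66% at the three means. Dropping patients unresolved at day 5 gives 31%, 59% and 87%. None of these restores 5%.

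**The case against.** The strongest reply is that the protocol never says it will compare means. It names no test for this outcome, allows a median as a summary and defers to an analysis plan that may well use Kaplan-Meier or Cox methods. This stands in part: the absence of a named test is no finding, and the error rates above are conditional on a comparison of means. But the window, the mean-based margin and size, and LOCF are stated, and an analysis plan faithful to them inherits the problem.

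The end of scoring is also inferred. The schedule figure is not shown, and the secondary outcomes include a post-treatment pain score, so a later reading may exist. This is why both caps are shown.

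LOCF is not said to extend scores past the scheduled end. The concern is therefore pressed for dropouts, not for patients who complete the course.

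A reader might infer three stronger points that the document does not support:
- *A product 1 day worse would usually pass.* This depends on the mean resolution time, which is not given. With a day-5 cap the rate exceeds 50% only from a reference mean of about 3.5 to 4 days; with a day-4 cap, from about 2.5 to 3 days.
- *The placebo comparison loses power.* Capping shrinks the SD too. With gamma times, SD 2.2 and a 1-day effect, power was about 96% uncapped and at least 99% capped. A loss appears under some Weibull inputs (94% to 59% at shape 2, mean 4, cut at 3.67 days), so the direction depends on the model.
- *An SD of 2.2 cannot fit the window.* A time bounded by T days has SD at most T/2. That is 2.0 for 4 days but 2.5 for 5 days, so 2.2 is possible on a 5-day window. It also comes from a previous study whose follow-up is not described.

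Finally, 84 does not set the trial's size; the 118 per group comes from the relief rate.

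**Conclusion.** The concern holds as an internal mismatch. The window and the rule of more than 24 hours make this primary outcome censored, while the sizing and the missing-data rule treat it as complete. If that is carried into a comparison of means with unresolved patients set to the window's end, the non-inferiority comparison of the two active arms loses its 5% error control. The false non-inferiority rate is about 11-72% with a day-5 cap and 28% to nearly 100% with a day-4 cap.

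These figures rest on gamma times with SD 2.2, 118 per arm, a true 1-day deficit and an assumed reference mean of 2 to 4 days. The direction is firm across the cases tested; the size is not, because the protocol gives no mean. The finding concerns the propellant comparison on this outcome and does not extend to the placebo comparison.

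**What to change.** - Remove LOCF for time to complete resolution.
- Count a resolution only when more than 24 hours at a score of 1 or less is actually recorded, and censor all other patients at their last confirmable reading.
- Analyse as time-to-event: Kaplan-Meier curves, and a Cox model stratified by centre with the baseline pain score as covariate.
- Restate the 1-day margin on that scale, as a hazard ratio or a difference in medians at a stated planning median, and replace the 84 per group by an event-based figure.
- State when scoring ends, so that the last confirmable onset is explicit.

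The cost is protocol and analysis-plan wording and one recalculation. The article reports that recruitment was still being prepared and that the analysis plan would be written before unmasking, so there is room for the change. The downside is that the margin is no longer a simple mean difference in days and needs a sentence of clinical explanation. Whether 118 per group still suffices should be checked against the event-based figure.

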#### Secondary outcome measures

Resolution rate of sore throat: proportion of patients who achieve complete resolution of sore throat.Time to relief of sore throat: length of time from the start of treatment until pain relief.Change of intensity of sore throat: assessed by visual analog scale from baseline to post-treatment.Change of traditional Chinese medicine syndrome score from baseline to post-treatment: each traditional Chinese medicine symptom is graded (Fig. 3), and the traditional Chinese medicine syndrome score is the accumulated score of the main symptom score and all minor symptom scores.

**Fig. 3 Fig3:**
[figure not shown]
Symptoms and signs score. TCM, traditional Chinese medicineChange of clinical signs score.

Three primary clinical signs in acute pharyngitis will be observed and recorded before and after treatment. The detailed scoring criteria are shown in Fig. 3.

### Safety outcome measures

Safety outcome measures include monitoring of adverse events, as well as clinical and laboratory findings. In addition to routine tests of blood, urine, and stool, hepatic and renal functions, and myocardial markers, electrocardiography will also be performed at baseline and again after treatment, to assess safety for each group. Patients will be required to record any unexpected symptoms or signs during the treatment period.

### Data management, monitoring, and auditing

A paper case report form will be used to collect data. To ensure maximum follow-up evaluation, the following measures will be taken:Train investigators and study staff in the importance of keeping participants in the trial until the end.Ensure that participants completely understand the research objectives and importance of completing the study.Keep contact information for participants including phone numbers, email addresses, and mailing addresses.Remind participants of their appointments.Make follow-up appointments at each participant’s convenience.Provide a remuneration of Chinese ¥200 after completing the study.Provide continued access to effective treatments after the trial for patients whose symptoms are not yet cured.Make efforts to obtain the participant’s consent for the collection of data outcomes when medication discontinuation occurs.

After completion of data collection, double data entry will be performed to transcribe the data into the computer database as soon as possible after recruitment and follow-up evaluation so that the patient and data collector are still available if responses are found to be missing or out of range. All information on the patients and outcome variables will be stored, updated, and monitored using EpiData3.1, which will also be used to format the data for statistical analysis. Regular backups and off-site storage will be conducted, to prevent loss of the database. The principal investigator, data managers, sponsor, and statisticians will confirm and lock the database prior to data processing. Only data managers and statisticians will have access to the final data. Original case report forms and any other records will be kept on file at each study site for 5 years.

Interim analyses will not be performed, as the investigational product is a registered and clinically used aerosol and the study is scheduled to last for approximately 6 months. An independent data monitoring committee will be set up to monitor patient safety and treatment efficacy data. Moreover, a monthly progress report on enrollment, recruitment, study participations, safety, and completion will be issued to the principal investigator. The regulatory authority at each study site and auditors independent of the investigators and sponsor will conduct a monthly audit, including, but not limited to, trial procedure and compliance with the protocol, standard operating procedures, code of Good Clinical Practice, and the applicable regulatory requirements. Any observation or finding should be documented.

### Adverse event reporting

An adverse event will be defined as any unfavorable and unintended sign (including abnormal laboratory findings), symptom, or disease temporally associated with the use of the study medication. All adverse events will be recorded in detail, including event, date of occurrence, grade, whether expected or unexpected, date resolved, and treatment patients receive specifically related to the event, and will be categorized as clearly not, doubtfully, may be, likely, or clearly related to the study medication. A serious adverse event will be defined as any untoward medical occurrence that, at any dose, results in death, is life-threatening, requires inpatient hospitalization or prolongation of existing hospitalization, results in persistent or significant disability or incapacity, is a congenital anomaly or birth defect, or other important medical event. Other events that are not likely to result in death, are not life-threatening, or do not require hospitalization, might be considered as serious adverse event if the event might jeopardize the patient and might require medical or surgical intervention to prevent one of the outcomes listed above.

Medically qualified investigators will record, assess, and report adverse events. Non-serious adverse events will be recorded in case report forms, and listed in a monthly progress report to the principal investigator and sponsor. Serious adverse events must be reported to the institutional review board, principal investigator, sponsor, and the Drug Registration Division of China’s State Food and Drug Administration and Research within 24 hours. The blinding procedures will be broken in case of a medical emergency.

### Sample size calculation

The sample size was calculated on the basis of the two primary outcomes, using ‘Non-inferiority tests for two proportions [differences]’ in PASS 11.0. Based on a previous study [22], the mean time to complete resolution of sore throat in both active treatments was similar, both with a standard deviation of 2.2 days. A difference of 1 day or more between groups was regarded a clinically important effect. Setting a one-sided *α* of 0.05 and *β* of 0.1, the sample size was estimated to be 84 cases for each group. Based on consultation with clinical experts and a preliminary unpublished study provided by the sponsor, the relief rate of sore throat in QWQYA with previous propellant was estimated at 91 %, with a difference of 10 % or more considered clinically significant. The sample size was estimated at 118 participants for each group, assuming a one-sided *α* of 0.05 and *β* of 0.15. Both the sample sizes were calculated according to the formula:

*n* = $$ {\left[\frac{2\left({Z}_{1-\alpha /2}+{Z}_{\beta}\right)\sigma }{\delta -\varDelta}\right]}^2 $$

Therefore, the final sample size for each group was 118 participants. Taking approximate dropout rates of 20 % into account, the number of participants to be recruited was estimated at 140 per group. Therefore, a total of 420 patients will be recruited in this trial.

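### Recruiting 140 per group covers about 15.7 % dropout on a requirement of 118, not the stated 20 %; per-protocol power for the relief rate is then about 83 %, not 85 %

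*Protocol article*

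**What the plan says.** All the figures stand in the protocol article under Sample size calculation. For the relief rate, "the relief rate of sore throat in QWQYA with previous propellant was estimated at 91" per cent, "with a difference of 10 % or more considered clinically significant", and the calculation was made "assuming a one-sided *α* of 0.05 and *β* of 0.15". The result of 118 exceeds the 84 per group found for time to resolution, so it sets the size of the trial: "the final sample size for each group was 118 participants". The next sentence moves to recruitment: "Taking approximate dropout rates of 20 % into account", "the number of participants to be recruited was estimated at 140 per group", and the total becomes 420.

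Three other sections bear on this step:

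- Withdrawal criteria rules out replacing patients who withdraw.
- Statistical analysis defines a full analysis set of everyone randomized, with last observation carried forward for missing primary outcomes, and a per-protocol set. Efficacy is analysed in both. The two active groups are compared by a non-inferiority test.
- Patient population and setting gives seven centres with 60 patients each, which also makes 420.

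**The concern.** An allowance for dropout is meant to leave the required number after the expected losses. Here 118 is the requirement and 20 % the expected loss, yet 80 % of 140 is less than 118. Because withdrawals are not replaced, nothing later in the trial makes up the difference.

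What is at stake is the power attached to the relief rate. The comparison that sets the sample size is the non-inferiority comparison of the two active aerosols, and for such a comparison the per-protocol result carries real weight. That is the analysis in which dropouts are lost. The line also fails a one-step check that any reader of the protocol can make.

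**Working it through.** **Inputs** (all from Sample size calculation unless noted)

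- Relief rate with the previous propellant: 0.91. The rate with the current propellant is not given separately; I assume it is also 0.91.
- The 10 % difference, read as the non-inferiority margin: 0.10.
- One-sided α = 0.05, so z = 1.645; β = 0.15, so z = 1.036.
- Dropout 0.20; recruited 140 per group.
- No replacement (Withdrawal criteria).

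**1. The plan's own figure.** With the unpooled normal approximation for a difference in proportions,

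n = 2 × p(1 − p) × (z₁₋α + z₁₋β)² / margin²
= 2 × 0.91 × 0.09 × (1.645 + 1.036)² / 0.10²
= 117.76 before rounding of the z-values, so 118.

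This matches the stated 118, so the inputs are read as the authors used them. The difficulty lies only in the dropout step.

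**2. The dropout step**

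- Correct inflation: 118 / (1 − 0.20) = 147.5, so 148 per group; 3 × 148 = 444 in total.
- Common but incorrect shortcut: 118 × 1.2 = 141.6, so 142 per group.
- In reverse: 140 × 0.80 = 112 evaluable per group.
- Dropout that 140 does cover: 1 − 118/140 = 0.157.

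Neither rule gives 140. Two shortfalls should be kept apart. In recruitment it is 148 − 140 = 8 per group (24 in total). In evaluable patients it is 118 − 112 = 6 per group.

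**3. Power for the relief rate**

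Power = Φ(0.10 / √(2 × 0.0819 / n) − 1.645), where 0.0819 = 0.91 × 0.09.

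| n per group | What it represents | Power |
|---|---|---|
| 112 | 140 recruited, 20 % lost | 83.4 % |
| 118 | stated requirement | 85.1 % |
| 140 | all recruited, none lost | 89.9 % |
| 148 | recruitment needed for 20 % dropout, none lost | 91.3 % |

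For n = 112: √(0.1638/112) = 0.03824; 0.10/0.03824 − 1.645 = 0.970; Φ(0.970) = 0.834. Exact binomial enumeration of the same test at 112 gives 83.5 %.

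**4. The other primary outcome.** For time to resolution (standard deviation 2.2 days, difference 1 day, one-sided 0.05, β = 0.1), the usual normal formula gives 83, against the stated 84. Either way, 112 evaluable patients per group are enough.

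**The case against.** The strongest reply is that the full analysis set does not shrink. It holds all randomized patients, and missing primary outcomes are filled by carrying the last observation forward, so 140 per group are analysed whatever the dropout. The nominal power there is about 90 %. This stands, and it limits the point to completers or the per-protocol set. It does not make the sentence right: the article inflates for dropout itself, which means that it treats 118 as the number left after losses. The 90 % also holds only if imputed outcomes behave like observed ones.

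A second reply is that the article calls the 20 % approximate, and that 420 equals seven centres of 60. A practical round total may well explain the figure, and it would be a fair reason. But the section does not give it; it presents 140 as the result of a 20 % allowance, and 15.7 % is more than a rounding away from that.

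A third reply is that 1.6 points of power is little. That is correct.

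A reader might go further and infer that 20 % dropout and 85 % power cannot both hold anywhere in this trial, or that the design is seriously underpowered. The documents support neither: one of the two planned efficacy analyses keeps 140 per group, and the loss in the other is small. A reader might also rework the power at a stricter one-sided level, prompted by the α/2 in the printed formula. The stated level is one-sided 0.05 and 118 reproduces at that level, so a lower figure obtained that way would reflect a different α and not the dropout step.

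**Conclusion.** The sentence is wrong as written. On a requirement of 118, a 20 % allowance needs 148 per group, and 140 allows for 15.7 %. If 20 % are lost, 112 per group remain, and power for the non-inferiority comparison on relief rate in the per-protocol analysis is about 83.4 %, which is 1.6 points below the stated 85 %. This is a minor arithmetic inconsistency with a small, confined effect; it gives no reason to doubt the trial's size in general.

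The result assumes equal true relief rates of 91 % in the two active groups, the 10 % difference as the margin, the normal approximation that reproduces 118, and a per-protocol set of exactly 112. The last is a simplification: the article does not say whether its 20 % includes patients who stay in the trial but breach the protocol, so the per-protocol set could be smaller.

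**What to change.** Keep 420 patients and restate the sentence in one of two ways:

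- 140 per group allows for about 15 % dropout on the requirement of 118; or
- with 20 % dropout, 112 per group are evaluable, giving about 83 % power for the relief rate at one-sided 0.05 in the per-protocol analysis.

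If 420 was set by the seven centres of 60, say so in the same place. The cost is one sentence and a slightly less favourable figure; conduct and analysis do not change. Recruiting 148 per group would also make the sentence true, but it takes 24 more patients to recover 1.6 points of power in one of the two analysis sets, which the size of the problem does not call for.
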